## Abstract

**Background::**

After the spread of the coronavirus disease 2019 (COVID-19) globally, upgraded quarantine and physical distancing strategy, strict infection measures, and government's strict lockdown have been abided to confront the spread of the COVID-19 in Thailand. During the COVID-19 pandemic, concerns about the mental health and psychosocial problems among health care workers and the general population are now arising. Yet, information on mental health and psychosocial problems among health care workers and the general population have not been comprehensively reported in Thailand. As such, we conduct a cross-sectional study, a national online survey to describe the short- and long-term consequences of the COVID-19 pandemic on mental health and psychosocial problems among health care workers and the general population in Thailand.

**Methods::**

This study is a repeated cross-sectional study, an open online voluntary national-based survey during the wave I (April 21–May 4, 2020) follow-up in the wave II (August 3–16, 2020), wave III (November 15–28, 2020), and a 1-year follow-up survey (wave IV: April 21–May 4, 2021) in Thailand. Health care workers at the hospitals and the adult general population will be invited to participate in the online survey via the SurveyMonkey that limits one-time participation per unique internet protocol address. The target sample size of at least 1182 health care workers and 1310 general populations will be required to complete the online survey for each wave of the survey. Sociodemographic characteristics and a set of measurement tools for mental and psychosocial problems for each subcohort including depression, anxiety, stress, resilient copings, neuroticism, perceived social support, wellbeing, somatic symptoms, insomnia, burnout (for healthcare workers), and public stigma toward COVID-19 infection (for the general population) will be collected. For all estimates of prevalence, we will weigh data for all wave analyses under the complex design of the survey. Subgroup analyses stratified by key characteristics will also be done to analyze the proportion differences. For the repeated cross-sectional survey, we will combine the data from the wave I to wave IV survey to analyze changes in the mental health status. We will perform multilevel logistic regression models with random intercepts to explore associations with individual-level and region-level/hospital-level predictors. We also plan to perform an ancillary systematic review and meta-analysis by incorporating data from our findings to all available evidence.

**Results::**

Our findings will provide information on the short- and long-term mental health status as well as the psychosocial responses to the COVID-19 outbreak in a national sample of health care workers and the general population in Thailand.

**Conclusion::**

This prospective, nationally based, a repeated cross-sectional study will describe the mental health status and psychosocial problems among health care workers and the general population in Thailand during the COVID-19 pandemic.

**Ethics and dissemination::**

Ethical approval for the study was obtained from the Faculty of Public Health and Faculty of Pharmacy, Chiang Mai University. The findings will be disseminated through public, scientific, and professional meetings, and publications in peer-reviewed journals.

**Thai Clinical Trials Registry (TCTR) registration number::**

TCTR20200425001.

## Introduction

1

After the spread of the coronavirus disease 2019 (COVID-19) globally, a patient was first reported, as a result, a community transmission has been rapidly evolved in Thailand. As of April 26, 2020, the COVID-19 caused 51 deaths of the 2922 confirmed cases, and 101 health care workers have been infected in both central and regional parts of Thailand.^[1]^ Based on the information concerning the confirmed cases, upgraded quarantine and physical distancing strategy, strict infection measures, and government's strict lockdown have been abided to confront the spread of the COVID-19 in Thailand.

Facing this large-scale infectious public health event, the ever-increasing number of confirmed and suspected cases, heavy workloads, negative emotions, depletion of personal protection equipment, lack of specific drugs, and feelings of being inadequately supported may all contribute the mental burden of health care workers.^[2]^ Meanwhile, confirmed and suspected cases of COVID-19 may experience fear of disease progression and the transmission to their family and friends. Concerns about the mental health and psychosocial problems among the general population are now arising owing to fear of contagion, perception of danger, widespread media coverage, financial problems, and unemployed related to the COVID-19 outbreak.^[3]^

Taken together, the infectious disease outbreaks, including the COVID-19 pandemic, can lead to the feeling of uncertainty, anxiety, and fear, and stigmatization in both health care workers and the general population who are under quarantine or at home. As such, it was postulated that the quarantined individuals, health care workers, as well as the general population are at risk of developing psychological distress and other mental health problems. To provide more advanced mental health care at the time of the pandemic, it is necessary to understand the mental health status and psychosocial problems of health care workers and the general population.

To our knowledge, however, little is known about how the COVID-19 pandemic may affect the mental health status and psychosocial problems of the health care workers and the general population in Thailand. Therefore, we will conduct a repeated cross-sectional study to understand the short- and long-term responses to the COVID-19 outbreak, examine the prevalence of mental health status, psychosocial related to the COVID-19 pandemic, and identify associated factors among a national sample of health care workers and the general population in Thailand.

## Objectives of the survey

2

To examine the prevalence of mental health and psychosocial problems among health care workers and the general population in Thailand during the COVID-19 pandemic.To document the changes over a 1-year follow-up of psychological response to a national infectious public health event.To identify early and late predictors of mental health status in response to the COVID-19 outbreak.To establish the prevalence of mental health status among health care workers and the general population worldwide during the COVID-19 pandemic.

## Methods

3

### Study design and time-period

3.1

The Health Outcomes and Mental Health Care Evaluation Survey: Under the Pandemic Situation of COVID-19 (HOME-COVID-19) is a repeated cross-sectional study, an open online voluntary national-based survey conducted during the wave I (April 21, 2020 to May 4, 2020) follow-up in the wave II (August 3, 2020 to August 16, 2020), wave III (November 15, 2020 to November 28, 2020), and wave IV—a 1-year follow-up survey (closed out: April 21, 2021 to May 4, 2021).

### Study population

3.2

The survey will use a convenient sampling and snowball strategies, and any health care workers (clinicians, nurses, and allied health staff [dentists, pharmacists, psychologists, occupational therapists, physiotherapists, case managers, and medical social workers]) working at the hospital and the general population in Thailand will be eligible for the online survey. The inclusion and exclusion criteria required for eligible participants are provided in Table 1.

**Table 1 T1:**

Eligibility criteria of the HOME-COVID-19 survey.

### Online survey conduct

3.3

With respect to the physical distancing strategy and minimize face-to-face interaction, we developed an online questionnaire via the SurveyMonkey (https://www.surveymonkey.com) that limits 1-time participation per unique internet protocol (IP) address. The researcher team will provide the relevant link or the Quick Response code (QR code) to all potential participants. For healthcare workers, all staff working at the hospital will be invited to participate in the online survey via the personal contact and healthcare community social media networks (email, LINE, Group of Messenger, Healthcare Professional Association) in Thailand. A convenience and snowball sampling strategy will be applied to recruit the general population through various social media networks including public websites, Facebook, LINE, Twitter, and Instagram. No reimbursement, other gifts, or payments will be offered for completing the questionnaire.

### Study instrument and questionnaire design process

3.4

The general population will complete a set of questionnaires, about participant characteristics and specific tool regarding the mental health and psychosocial question. Also, health care workers will complete a separate set of questions. The survey questionnaire, written in Thai, comprised 13 main components. There are different types of questions in the questionnaire including (yes/no) questions, the Likert scale, multiple-choice questions, and open-ended questions.

The questionnaire will be carefully revised by a panel of health care professionals that include 3 epidemiologists, 2 psychiatrists, 1 social scientist, and 2 hospital directors. The questionnaire will be further validated by a pilot survey of 30 health care professionals and 30 general populations. This validation process is used to measure the time needed to complete the questionnaire and assure that all the questions and sections of the questionnaire are phrased clearly and appropriately for comprehension.

Baseline sociodemographic characteristics include age, sex, educational level, marital status, religion, occupation/profession status, the region of residence/hospital, living status, number of a household family member, monthly income, job/income loss related to COVID-19 outbreak, financial problems, reimbursement schemes, comorbidities, media exposure, working from home information, quarantine/isolation information, willingness to quarantine/work during COVID-19 outbreak, global rating scale on the degree of fear to COVID-19, self-rated level of preparedness, and resilience capability against the COVID-19 outbreak. For health care workers, a constructed questionnaire is carried out using the established framework of hospital disaster resilience through existing literature^[4,5]^ and consultation with experts. These included the availability and adequacy of personal protective equipment and detailed information on hospital-level or capability related to COVID-19 outbreak and management.

A set of measurement tools for mental health and psychosocial problems for each subcohort are described in Table 2. We will focus on symptoms of depression,^[6]^ anxiety,^[7]^ stress,^[8]^ resilient copings,^[9]^ neuroticism,^[10]^ perceived social support,^[11]^ well-being,^[12]^ somatic symptoms,^[13]^ insomnia,^[14]^ burnout (for health care workers),^[15]^ and public stigma toward COVID-19 infection (for the general population), using a Thai version of validated measurement tools or our team development version tools. Detail of participants’ timeline and assessment for each wave of the survey is illustrated in Table 3.

**Table 2 T2:**
[figure not shown]
Measurement tools of the HOME-COVID-19 survey.

**Table 3 T3:**
[figure not shown]
Schedule of measurement for each wave of the HOME-COVID-19 survey.

## Statistical analysis plan

4

### Sample size and power calculation

4.1

The target sample size of participants was estimated based on the previous studies among health care workers or general population under the COVID-19 outbreak: prevalence of mental health problems (depression, anxiety, stress, and psychological distress) with a range of 5.2% to 71.5%^[16–25]^ and 3.3% to 75.5%^[20,22,23,26–31]^ for health care workers and the general population, respectively. To compensate for a design effect of 2.0 and a completed responses rate of 60%, a target of at least 1182 health care workers and 1310 general populations is required to complete the online survey for each wave of the survey to ensure a power of 80% and a 0.05 type I error. However, there will be no restriction on the number of participants in this online survey.

### Data management

4.2

The collected data will be organized by the Google Form and collected in an Excel spreadsheet. The online survey will be completely anonymous and uploaded to a Google Drive encrypted by a password. Only the management team can access all data. Data entered into the Google Form will be quality-checked by a researcher to ensure accuracy. All steps involved in the approach to data management will be independently conducted by 2 data administrators from the Pharmacoepidemiology and Statistics Research Center (PESRC).

### Statistical analysis

4.3

Data synthesis will be conducted separately for health care workers and the general population. Descriptive data statistic will be summarized as number (percentage) or mean ± standard deviation, or median with an interquartile range as suitable. Differences in responses with respect to baseline characteristics will be assessed using Fisher exact test and unpaired *t* test or Wilcoxon rank-sum test for categorical and continuous data, respectively.

For all estimates of prevalence, we will weight data for all wave surveys (wave I, II, III, and IV) analyses under the complex design of the survey—weighting adjusted for noncompleted responses survey and national rates of unemployment at the time of each survey. Population control totals for age by sex and region, and the rate of internet use will be obtained from the National Statistic Office, Ministry of Information and Communication Technology, Thailand. The estimates of the prevalence of mental health status will be calculated and reported along with the 95% confidence intervals (CIs). Subgroup analyses stratified by key characteristics (eg, age, sex, region, working position [frontline or nonfrontline], hospital type, and region of residence) will also be done to analyze the proportion differences.

Moreover, an online wave II, III, and a 1-year follow-up survey will be compared to assess the long-term responses and resilience capability on the prevalence of mental health status among health care workers and the general population. Nonoverlapping 95% CIs are indicating statistical differences in the prevalence between the survey wave or subgroups, with the *P* values that are based on the trend tests. The absolute change in prevalence will be calculated with the formula: Δ = (1/duration between survey) × (p_last_ – p_initial_), with variance estimated as (var [p_last_] + var [p_initial_])/(duration between survey), where p_last_ and p_initial_, stand for the last prevalence and initial prevalence, respectively. Trend analysis will be performed to identify the effect of overtime across the study time frame.

For the survey—wave I, the crude association between participant characteristics will be assessed through the univariable logistic regression models to identify the candidate risk factors of early mental health problems. Subsequently, risk factors with a *P* value <.100 were then included in the multivariate logistic regression analysis with the stepwise backward method. The final model was also determined for multicollinearity by investigation of the variance inflation factors of the risk factors within the multivariable model. The effect estimates of the final risk factors model for mental health problems will be expressed as odds ratios (ORs) with corresponding 95% CIs.

For the repeated cross-sectional survey, we will combine the data from the wave I to wave IV survey to analyze changes in the mental health status. We will perform multilevel logistic regression models with random intercepts to explore associations with individual-level and region-level/hospital-level predictors. The survey wave will be analyzed as a level 1 variable with a fixed effect to distinguish between study survey waves across the study time frame.

To improve the generalizability of study findings, we also plan to perform an ancillary systematic review and meta-analysis by incorporating data from our findings to all available evidence regarding the mental health and psychosocial problems among health care workers and the general population. The prespecified protocol for systematic review has been registered in the International Prospective Register of Systematic Reviews (PROSPERO: registration number, CRD42020177120). Globally, the mental health problems attributable to the general population during the COVID-19 pandemic will be estimated by multiply the pooled prevalence of our findings against the United Nations’, world population report.

Missing data or noncompleted responses will be excluded from the primary analyses. However, a multiple imputation method will be performed in the sensitivity analysis. All analyses will be performed using Stata software version 14.0 (StataCorp, LP) and Microsoft Excel version 2016. They will be 2-tailed and *P* value <0.05 will be considered statistically significant.

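### The single weighting rule for all prevalence estimates makes no exception for hospital health care workers, so on its natural reading they would be calibrated to the general public

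*Protocol article*

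**What the plan says.** All of the weighting text is in the protocol article, section 4.3 (Statistical analysis).

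- Scope: "For all estimates of prevalence, we will weight data for all wave surveys (wave I, II, III, and IV) analyses". No study group is excepted.
- Adjustments: "weighting adjusted for noncompleted responses survey and national rates of unemployment at the time of each survey".
- Control totals: "Population control totals for age by sex and region, and the rate of internet use will be obtained from the National Statistic Office". No total for the health workforce (profession, hospital type or similar) is named.
- Separation of groups: "Data synthesis will be conducted separately for health care workers and the general population".

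Section 3.2 (Study population) defines the first group as clinicians, nurses and allied staff "working at the hospital and the general population in Thailand will be eligible for the online survey". Section 3.3 (Online survey conduct) repeats that "all staff working at the hospital will be invited to participate in the online survey". Section 4.1 allows a design effect of 2.0 and sets a minimum of 1182 completed health care worker responses per wave.

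**The concern.** The two groups have different target populations. For health care workers the target is hospital staff, who are employed by definition. For the general population it is the adult public. One set of public margins cannot serve both.

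The paragraph that holds the rule also lists subgroups that exist only among health care workers (frontline status, hospital type). It therefore governs their estimates too. If it is followed as written, the result estimates prevalence in a hypothetical workforce with the age, sex and regional mix of the whole country.

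Health care worker prevalence is one of the two quantities in the first objective (section 2). It also feeds the comparisons between waves and, through the planned meta-analysis, the pooled estimates.

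**Working it through.** **The plan's own figure.** Section 4.1 gives 1182 health care workers and 1310 members of the public. Undoing the stated inflation gives 1182 × 0.6 / 2 = 354.6 and 1310 × 0.6 / 2 = 393. The section gives ranges of prevalence but no single prevalence, detectable difference or precision, so neither target can be reproduced from its inputs. The point does not depend on this. Only 1182 and the design effect of 2.0 are used below.

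**Step 1: unemployment margin.** Let U be the national unemployment rate. The raking factor for the unemployed cell is U divided by the sample share unemployed. Among hospital staff that share is 0, so the factor is U/0 and is undefined for any U above 0. If the adjustment is instead a constant c applied to everyone, Σ(c·w·y)/Σ(c·w) = Σ(w·y)/Σ(w), so c cancels. It cancels from the Kish factor n·Σw²/(Σw)² in the same way. The margin is inapplicable to this group, but it does not itself create bias or extra variance.

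**Step 2: age, sex and region totals.** Let P be a cell's share in the public, s its share among health care workers (sample assumed to match the workforce), and π the prevalence in the cell.

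- Bias against the workforce prevalence = Σ(P − s)·π
- Kish variance factor = Σ P²/s

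The bias is zero if P = s in every cell or if π is the same in every cell. The Kish factor exceeds 1 whenever P and s differ.

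**Step 3: illustration by sex.** All shares and prevalences here are assumed; none is in the documents. The public is taken as 51% women, with higher prevalence in women.

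| Women among staff | Kish factor | Effective n from 1182 | Bias, 10-point gap | Bias, 15-point gap |
|---|---|---|---|---|
| 60% | 0.51²/0.60 + 0.49²/0.40 = 1.03 | 1143 | −0.9 | −1.35 |
| 78% | 0.51²/0.78 + 0.49²/0.22 = 1.42 | 830 | −2.7 | −4.05 |
| 85% | 0.51²/0.85 + 0.49²/0.15 = 1.91 | 620 | −3.4 | −5.1 |

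With no gap between the sexes the bias is 0; with the gap reversed it is positive. As a worked case, take 35% in women and 20% in men with 78% women. Workforce prevalence is 0.78 × 35 + 0.22 × 20 = 31.7%. Weighted to the public it is 0.51 × 35 + 0.49 × 20 = 27.65%.

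**Step 4: adding age.** Again all shares are assumed.

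- Aged 60 or over, 5% of staff against 18% of adults: 0.18²/0.05 + 0.82²/0.95 = 1.36
- Aged 60 or over, 2% of staff against 22% of adults: 0.22²/0.02 + 0.78²/0.98 = 3.04

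If sex and age are independent in both populations (a further assumption), the factors multiply. With 78% women, 1.42 × 1.36 = 1.93 (effective n about 610) and 1.42 × 3.04 = 4.3 (effective n about 273). Over the full range of sex shares the product runs from 1.03 × 1.36 = 1.40 to 1.91 × 3.04 = 5.8, so the assumed cases fall on both sides of 2.0.

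**The case against.** The strongest reply is that the protocol never states that the national totals are applied to the health care worker file. It says only that they will be obtained, and it opens the section by separating the two groups. Group-specific weights are compatible with that, and a journal article may leave the allocation of totals to a fuller plan. This stands in part: the application to health care workers is the natural reading, not an explicit statement. But separating the analyses does not supply a second weighting target. The rule is written for every prevalence estimate, and the only sources named are national. The point concerns a stated rule that misfits one group, not absent detail.

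A reader might also infer any of the following, which the documents do not support:

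- **That the health care worker estimates are certainly biased, and downwards.** Direction and size depend on workforce composition and on prevalence by cell, and neither is given.
- **That the unemployment adjustment is itself a source of bias or variance.** Step 1 shows only that it is inapplicable.
- **That the variance must exceed the planned design effect.** Sex alone stays below 2.0 in every case shown, and so do some sex-and-age cases. Section 4.1 does not say which components its 2.0 covers.
- **That the bias equals a planned margin of ±4 points.** No precision target is stated. About 4.0 points appears only by back-calculation with an assumed prevalence of 50%: 1.96 × √(2 × 0.25/1182) = 0.040.

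**Conclusion.** The concern holds in conditional form. As written, section 4.3 applies one weighting rule to both groups, and that rule does not fit health care workers. The unemployment margin has no meaning for them, and the other named totals describe a different population. If those totals are applied, health care worker prevalence can be biased and less precise.

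The size cannot be determined from the documents. Under the assumed compositions, weighting on sex alone gives roughly 0 to −4 points (−5.1 at the most extreme pairing shown) and a Kish factor of 1.03 to 1.91, within the planned 2.0. Adding age can take the factor past 2.0 if few staff are aged 60 or over. The general-population survey is not affected by this point.

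**What to change.** In section 4.3, state the weighting target for each group.

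- Restrict the unemployment, internet-use and national age, sex and region totals to the general-population survey. The noncompletion adjustment can stay for both groups.
- Weight the health care worker survey to hospital workforce totals, for example profession by region or by hospital type, with sex and age where available.
- If no such totals can be obtained, report that group without population calibration and label the result a sample estimate.

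The cost is a few sentences of analysis text and one request for workforce totals. The downside is small: workforce margins may be coarser than census margins. If separate weights were already intended, one sentence saying so, with the source of the workforce totals, settles the point.

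### Judging wave and subgroup differences by non-overlap of two 95% CIs is stricter than the stated 0.05 level, and the trend-test P values do not test the same contrasts

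*Protocol article*

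**What the plan says.** All of this is in the protocol article.

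- **Prevalence (section 4.3, Statistical analysis).** Weighted prevalence estimates "will be calculated and reported along with the 95% confidence intervals (CIs").
- **Decision rule (same section).** For comparisons of those prevalences: "Nonoverlapping 95% CIs are indicating statistical differences in the prevalence between the survey wave or subgroups". The P values that go with it are "values that are based on the trend tests".
- **Level (end of section 4.3).** Of all analyses the article says "They will be 2-tailed", and a P "value <0.05 will be considered statistically significant".
- **Planning (section 4.1, Sample size and power calculation).** The targets of 1182 health care workers and 1310 members of the general population per wave are set "to ensure a power of 80% and a 0.05 type I error". No difference, and no pair of waves or subgroups, is named for that power.
- **Other analyses in section 4.3.** There is an absolute change per unit time with a variance, and a multilevel logistic model on the pooled waves with survey wave as a fixed effect. Neither is named as the criterion for differences in weighted prevalence.

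**The concern.** Checking whether two separate 95% intervals overlap is not a 5% test of their difference. It compares the difference with the sum of the two half-widths. A test of the difference uses the standard error of the difference, which is smaller than the sum of the two standard errors. So the stated rule and the stated significance level disagree.

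The P values do not close the gap. A trend test asks whether prevalence moves steadily over ordered categories. It does not ask whether two given waves differ, it can miss a rise followed by a fall, and it does not compare unordered groups with more than two levels, such as region. One comparison could therefore carry two conflicting verdicts.

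At stake is the second objective, change over one year, together with the subgroup contrasts such as frontline against nonfrontline staff. The article wants its findings to inform public policy, and there a missed difference is the costly error.

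**Working it through.** **Plan's own figure.** The targets of 1182 and 1310 cannot be reproduced or refuted. Section 4.1 gives prevalence ranges, a design effect of 2.0 and a 60% completion rate, but no single prevalence, difference or precision. Many assumed inputs land near the targets. The results in the table below do not depend on the sample size.

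**Inputs.** Each interval is 95%, so z = 1.96 (section 4.3). The level is 0.05 two-tailed (section 4.3). The reference power is 80%, for which z = 0.8416. Independence between estimates is assumed, as in the article's own variance for the change, which adds two variances with no covariance term.

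**Thresholds.**

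- Non-overlap requires |p1 − p2| > 1.96 × (SE1 + SE2).
- A direct test requires |p1 − p2| > 1.96 × √(SE1² + SE2²).
- With r the ratio of the standard errors, non-overlap is a z test with threshold c = 1.96 × (1 + r)/√(1 + r²).
- Actual level = 2 × (1 − Φ(c)).
- Power, where a direct test has 80%, = Φ(1.96 + 0.8416 − c).

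For r = 1: c = 1.96 × 2/√2 = 2.772; level = 2 × (1 − Φ(2.772)) = 0.0056; power = Φ(2.802 − 2.772) = 51.2%.

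| SE ratio r | Approximate ratio of n | c | Actual level | Power |
|---|---|---|---|---|
| 1 | 1:1 | 2.772 | 0.0056 | 51.2% |
| 1.5 | 2.25:1 | 2.718 | 0.0066 | 53.3% |
| 2 | 4:1 | 2.630 | 0.0085 | 56.8% |
| 3 | 9:1 | 2.479 | 0.0132 | 62.6% |
| 5 | 25:1 | 2.306 | 0.0211 | 69.0% |

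Equal standard errors are a fair reference for waves, since every wave has the same minimum target. Subgroups may be far from equal. Positive correlation between the estimates makes the rule stricter: with equal standard errors, a correlation of 0.1 gives 0.0035 and 45%, and 0.3 gives 0.0009 and 30%. With equal standard errors and independence, non-overlap would match a 0.05 test only for intervals of about 83.4%.

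**Simulation.** One million binomial runs used an effective size of 591 per wave (1182/2, treating 1182 as completed responses). The rule's error rate was 0.0058 at 30% prevalence and 0.0057 at 50%, against 0.051 for the direct z test. Its power was 51.7% for 30% v 37.7% and 51.4% for 50% v 58.1%, where the direct test had 80%.

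**Two illustrations of conflicting verdicts**, with assumed prevalences and effective n = 591:

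1. *30% v 37%.* The standard errors are √(0.30 × 0.70/591) = 0.0189 and √(0.37 × 0.63/591) = 0.0199. The intervals 26.3–33.7% and 33.1–40.9% overlap, so the rule flags nothing. The direct test gives z = 0.07/√(0.0189² + 0.0199²) = 2.56, P = 0.011.
2. *Waves at 30%, 40%, 40%, 30%.* The first two intervals, 26.3–33.7% and 36.1–43.9%, do not overlap, so the rule declares a difference. A linear trend over equally spaced waves has contrast −3(0.30) − 0.40 + 0.40 + 3(0.30) = 0. On the actual start dates (days 0, 104, 208 and 365) z is about −0.5. The trend P value would show nothing.

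**The case against.** The best defence is that the sentence gives a sufficient sign of a difference and does not say that overlap means no difference. Read that way it is valid: for independent estimates, non-overlap implies P < 0.05. This much stands, and a reader who infers that every real change will be reported as absent goes beyond the text. It does not rescue the rule, because no other pairwise criterion is attached to the weighted prevalences.

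Second, the multilevel model already contains wave as a fixed effect. If wave is entered as a category (the coding is not stated), the model can supply direct wave contrasts and a joint test. This also stands and makes the repair easy, but the article does not make that model the criterion for these differences.

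Third, a reader might infer that trend tests are to be run across sex, region and hospital type. The wording is ambiguous: the same paragraph later describes trend analysis as concerning time, so trends over waves within subgroups may be meant. In that case the P value does not compare subgroups at all. If trend across subgroup levels is meant, then for a two-level factor such as sex it reduces to an ordinary two-group test and is harmless. The objection holds for unordered factors with more than two levels.

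Finally, with many outcomes and subgroups a strict rule may look welcome. But its level shifts with the ratio of the standard errors, so it does not control error at any chosen value.

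**Conclusion.** The concern holds, with moderate severity. For independent estimates the overlap rule works at a level of about 0.006 with equal standard errors, 0.009 at a ratio of 2 and 0.013 at 3, against a stated 0.05. A difference that a direct test would detect with 80% power is detected with about 51%, 57% and 63% respectively.

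Two stronger readings are tempting and not supported. One is that the study's own 80% power drops to 51%. Section 4.1 names no comparison for that power, so the 51% is a loss relative to a direct test, not a recalculation of the design. The other is that 0.006 applies to every comparison. It needs equal standard errors, which is plausible for waves at target size. It need not hold for subgroups, or for waves whose sizes drift apart, since recruitment has no cap.

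The rule produces no excess of false positives per comparison. The harm is missed differences, and verdicts from the intervals and the trend P values that can point in opposite directions. The prevalence estimates and their intervals, which serve the first objective, are unaffected.

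**What to change.** Delete the non-overlap rule from section 4.3 and replace it with the following.

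- **Two waves or two subgroups:** the difference in weighted prevalence with its 95% CI and a design-adjusted Wald test at two-tailed 0.05.
- **Nominal subgroups with more than two levels:** a design-adjusted (Rao-Scott) chi-square test.
- **Waves overall:** a joint 3-df test with wave as a categorical term. The planned multilevel model can also supply this if the categorical coding is stated.
- **Trend:** a linear trend on calendar time, reported as supplementary. The starts of the waves are 104, 104 and 157 days apart, so wave number is not a substitute for time.

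The cost is a few sentences of analysis text and standard survey commands in the software already named. No new data or change in sample size is needed.
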